## **5.3 Research protocol**

### 5.3.1 Description of the visits

Upon awakening the day of a study visit, participants will be asked to swallow an ingestible telemetric pill which will have been provided to them beforehand. Upon arrival to the laboratory, participants will be asked to provide a urine sample and weigh themselves nude (in private). Participants will then be instrumented following which they will rest in the seated position for a 10 min baseline period at a room temperature of 24°C. Following this baseline period, they will enter an environmental chamber maintained at either 38°C and 60% RH or 46°C and 10% RH and will be seated within a semi-recumbent mesh chair that will allow for convective airflow. Participants will remain seated for 3 hours within the environmental chamber while the relevant cooling intervention is administered. During the exposure, heart rate will be measured continuously from an ECG signal and blood pressure measurements will be taken every 20 minutes by automated auscultation of the brachial artery. Rate pressure product (**RPP**) will subsequently be calculated at baseline and every 20 minutes during the 3 hour exposure (see arrows in timeline below). Participants will be provided with 200 ml of water every 20 minutes. At the end of the 3 hour period, participants will exit the environmental chamber to be de-instrumented and will be asked to weigh themselves nude in private to calculate whole-body sweat rate. During the study visits with fan use, an 18” diameter fan will face the participant from a distance of 1.0 m to provide an airflow of 4.0 m/s. During the study visits with skin wetting, tap water (~18°C) will be applied every 10 minutes to the forehead, face, arms and neck using a cloth.

[figure not shown]

### 5.4 Measurements

- 1) Body weight will be measured during the preliminary visits, as well as before and at the end of each study visit with a scale.
- 2) Body height will be measured during the preliminary visit with a stadiometer.
- 3) Blood samples will be drawn from a sterile catheter inserted into a peripheral vein.
- 4) Heart rhythm will be acquired during the preliminary visits, as well as continuously during the study visits from an ECG signal. Heart rate will also be measured continuously during the study visits with a monitor placed around the chest.
- 5) Blood pressure will be measured during the preliminary visits, as well as every 20 minutes during the study visits by automated auscultation of the brachial artery.

- 6) Internal body temperature will be measured continuously during the study visits with an ingestible telemetric pill.
- 7) Oral temperature will be measured by placing an oral thermometer under the tongue.
- 8) Skin temperatures will be measured continuously during the study visits by taping sensors to the skin surface.
- 9) Local sweat rate will be measured continuously during the study visits using plastic capsules attached to the skin surface and ventilated with dry air.
- 10) Skin blood flow will be measured continuously during the study visits on the forearm by laser-Doppler flowmetry.
- 11) Cardiac output will be measured every 20 minutes during the study visits with an inert gas rebreathing technique.
- 12) Urine specific gravity (as a measure of hydration status) will be determined from a urine sample collected at the beginning of each study visit.
- 13) Thermal comfort and sensation will be measured every 20 minutes during the study visits using visual scales.

| Measurements                  | Preliminary visit | Laboratory visits |
|-------------------------------|-------------------|-------------------|
| Information and consent       | X                 |                   |
| Familiarization               | X                 |                   |
| Medical history               | X                 |                   |
| Body height                   | X                 |                   |
| Blood sample                  | X                 | X                 |
| Body weight                   | X                 | X                 |
| Heart rate and rhythm         | X                 | X                 |
| Blood pressure                | X                 | X                 |
| Internal body temperature     |                   | X                 |
| Oral temperature              |                   | X                 |
| Skin temperatures             |                   | X                 |
| Local sweat rate              |                   | X                 |
| Skin blood flow               |                   | X                 |
| Cardiac output                |                   | X                 |
| Urine specific gravity        |                   | X                 |
| Thermal comfort and sensation |                   | X                 |

## 6- Statistics

### 6.1 Sample size

The sample size computation is based on comparison of the primary endpoint (change in rate pressure product from baseline to the end of a 3 hour simulated heatwave exposure to 38°C and

60% RH) between the 4 conditions of control, fan use alone, skin wetting alone, fan use + skin wetting.

The mean and standard deviation of the change in rate pressure product were taken from the preliminary data presented in Figure 3 and are expected to range between 1000 bpm x mmHg and 1700 bpm x mmHg for the mean and between 1700 bpm x mmHg and 2000 bpm x mmHg for the standard deviation. The standard deviation of the difference between conditions is expected to be similar.

The main interest is to compare the control condition with the 3 other conditions taken individually, which implies a significance level of 0.0167 ( $0.05 / 3$ ). A difference of 1250 bpm x mmHg in change in rate pressure product between the control condition and any other condition is judged to be clinically relevant.

In this context a sample size of 30 participants will give 80% power to detect a difference of 1250 bpm x mmHg in change between the control condition and any other condition, assuming that the standard deviation of the difference between conditions is 2000 bpm x mmHg and using a paired t-test with a 0.0167 two-sided significant level. To account for an approximately 10% loss to follow-up rate, 34 participants will be included in the study. Of the 34 participants, 17 will be taking beta-blockers whereas the other 17 will not be taking beta-blockers.

## *6.2 Statistical analysis*

Study variables will be presented using descriptive statistics. Mean, standard deviation, median, minimum and maximum will be presented for continuous variables. Number and percentage will be presented for categorical variables. Statistical assumptions underlying planned statistical tests will be examined and data transformation or non-parametric analysis might be used if appropriate. All statistical tests will be conducted at the 0.05 significance level unless specified otherwise.

Primary analysis: A one-way repeated analysis of variance (ANOVA) model will be used to compare the primary endpoint (change in rate pressure product under the 38°C and 60% RH heatwave exposure) between the conditions of: control, fan alone, skin wetting alone and fan + skin wetting. Contrasts under this model will allow for the three main comparisons:

- Control vs. fan alone
- Control vs. skin wetting alone
- Control vs. fan + skin wetting

These three comparisons will be tested at the 0.0167 significance level to control for the multiplicity of tests. This will be considered as the primary analysis of the study.

Since rate pressure product will be measured several times during the 3 hour simulated heatwave exposure, a two-way repeated measures ANOVA model on rate pressure product, having a term for condition, a term for time and a term for the condition x time interaction, might also be used to more precisely describe the pattern of change over the 3 hours of heat exposure across the conditions.

Secondary analysis: The change in rate pressure product from start to end of a 3 hour simulated heatwave exposure at 46°C and 10% RH will be compared between the control and skin wetting conditions using a paired t-test.

Exploratory analyses: To study the impact of beta-blockers, repeated measures ANOVA models on change in rate pressure product with a term for condition, a term for beta-blockers (yes/no) and a term for the interaction between condition and beta-blockers will be used for each heatwave condition. Other tertiary endpoints measured throughout the 3 hour exposures will be analyzed for each heatwave condition with a two-way repeated measures ANOVA model, having a term for condition, a term for time and a term for the condition x time interaction.

## **1- Outline the theoretical, empirical and/or conceptual basis, background evidence for the research proposal with relevant literature.**

The frequency, intensity and duration of heat waves are increasing globally (Bi et al. 2011), and with these increases we can expect with a high level of certainty a parallel rise in heat-related morbidity and mortality (Hajat, O'Connor & Kosatsky, 2010). In an attempt to combat this, there is a need for evidence-based guidelines to be made available that educate people on the steps they can take to protect themselves during extreme heat events. One particular population group at a disproportionately higher risk of morbidity and mortality during these extreme weather events is the elderly (Hajat, O'Connor & Kosatsky, 2010). Therefore, it is of great importance to make targeted recommendations for this population. Air-conditioning is the best protection during extreme heat events, but it is not accessible to many of the most vulnerable populations and widespread use and reliance on it during extreme heat events can cause blackouts (Kaiser et al., 2001; Semenza et al., 1996). Researchers began examining the effectiveness of using a fan as a cooling intervention and found that public health recommendations regarding fan-use were not uniform between agencies and often not evidence-based (Jay et al., 2015). If fan-use were to be found effective, it would provide a low-cost solution with a low-energy requirement. Research to date suggests that the benefits of fans have been greatly underestimated by public health agencies (Jay et al., 2015). Despite organizations such as the WHO, EPA and the Government of Victoria advising against using fans in hot conditions, a study published in the Journal of the American Medical Association (JAMA) demonstrated that fan use reduced physiological strain in young healthy men in simulated hot/humid heat wave conditions (Ravanelli et al., 2015). The use of a fan increased airflow which improved sweating efficiency and led to greater evaporative heat loss. The effectiveness of fan-use does depend on both the unique environmental conditions and the individual; it has been suggested that in certain conditions fans may be less effective and even harmful to older adults due to age-related decrements in sweating (Gagnon et al., 2016). Due to the findings to date it is clear that there is a need for evidence based recommendations specific to both the environmental conditions and population-specific, particularly those populations who have compromised thermoregulatory ability, such as the elderly. In a recent article by Jay and Capon (2017) it was proposed that external skin wetting could be used by the elderly to compensate for their decreased sweating ability, while still gaining the benefits of increased latent heat loss as a result of improved evaporative efficiency with fan-use. This combination has the potential to be a simple, cost-effective cooling intervention that has 50-times lower cost and electricity requirement than air conditioning and so therefore can be utilized by vulnerable populations in a low-resource environment. We propose the below study to examine if fan-use, in combination with skin-wetting can be an effective cooling strategy that is able to decrease the physiological strain experienced by elderly during heat waves, and as a result decrease their chance of experiencing an adverse cardiovascular event. During the 2003 heat wave in Lyon, France, antihypertensive use was associated with a 177% increased risk of mortality in adults presenting to the emergency department with heat stroke (Argaud et al., 2007). Due to this historical evidence and the prevalence of hypertension in older adults, it is important to include older adults on antihypertensives in our study to adequately represent the older adult population, while also investigating the impact of antihypertensive use on individuals' responses to simulated heat wave exposure and the proposed interventions. We believe the proposed project will provide evidence

that will help public health and government organizations make evidence-based environment and population specific recommendations for older adults during heatwaves.

## **2- Outline the methodology for the research proposal including:**

### *2.1. Research Questions:*

The primary research question guiding this project is: Are fans and/or skin wetting effective in decreasing the physiological strain experienced by elderly during a simulated hot humid heatwave (38°C with 60% relative humidity).

The secondary research question guiding this project is: are fans and/or skin-wetting effective in decreasing the physiological strain experienced by elderly during a simulated hot, dry heatwave (45°C with 15% relative humidity).

### *2.2 Research hypotheses:*

The research hypotheses for this study are:

3. In the hot and humid condition, all interventions will result in improved cooling compared to the control (no-fan) trial. With fan and skin-wetting (FSW) being the most effective, then no fan and skin-wetting (NFSW), then fan (F), and finally, the control, no-fan (NF).
4. In the very hot and dry condition, skin wetting with no fan (SWNF) will be the most effective cooling intervention followed by fan and skin-wetting (FSW). We expect the fan (F) intervention to be less effective than the control, no-fan (NF).

*4.3 Participant characteristics:* To complete this study, 56 (greater than or equal to 60 years) adults will be recruited from previous participants who have consented to being contacted for future studies and through the distribution of recruitment flyers at both the Cumberland and Camperdown campuses at The University of Sydney.

*4.4 Sample size:* The sample size computation is based on comparison of the primary endpoint (change in rate pressure product from baseline to the end of a 2 h simulated heatwave exposure to 38°C and 60% relative humidity) between the 4 conditions of control, fan use alone, skin wetting alone, fan use + skin wetting. This preliminary data from young healthy participants was provided by [name], a former PhD student from within our laboratory. A non-repeated measures ANOVA on this data demonstrates 20% (eta squared of 0.2) of the variability was due to the intervention. Using GPower 3.1.9.2 software, an ANCOVA: Fixed effects, main effects and interactions f-test was performed using an alpha of 0.05, beta of 0.1 and an effect size of 0.5 to determine a total sample size of 45 is needed to obtain sufficient statistical power. To account for approximately 20% loss to follow up, 56 participants will be included in the study. Of the 56 participants, 14 will be healthy older females, 14 will be healthy older males, 14 will be healthy females taking antihypertensive medication, and 14 will be older males taking antihypertensive medication.

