- Cardiac Stress Test: The participant will undergo a physician-supervised graded exercise test on a treadmill while undergoing ECG and blood pressure monitoring. Both are described below.

- Venepuncture: If determined necessary by the study physician, a blood sample will be obtained by peripheral puncture of the forearm vein during their second preliminary session. Venepuncture will be performed by personnel with phlebotomy training.

If the participant agrees to participate in this study, they will undergo testing at the Camperdown Campus of the University of Sydney for approximately 4 hours on 4 separate occasions. (There is an option to participate in an additional four experimental sessions.) Each experimental session will be separated by at least 72 hours. Participants will be asked to abstain from alcohol and caffeine, avoid strenuous exercise in the 12 h prior to each experimental session, and will be instructed to consume a light meal and 0.5L of water ~2 h before arriving at the lab. They will be provided with a standardized singlet and shorts to wear and will undergo 30-min of baseline rest (seated) in a thermoneutral room (~24°C), where they will be instrumented using the equipment described below. After 30-min, they will then enter a climate-controlled chamber, where they will be seated unrestrained in a standard armchair for the remainder of the 3-hour experimental protocol. This protocol will consist of the participant sitting in a 38°C and 60% relative humidity room. (If they choose to participate in the additional four trials the conditions will be 45°C and 15% relative humidity). During each session the participant will undergo one of the following four conditions: no cooling intervention, use of an electric fan, self-wetting the skin with a sponge, or use of an electric fan while self-wetting the skin with a sponge. Additionally, in all trials they will be provided with 3ml per kg of cold (~18°C) water every hour. In all fan trials, they will be seated 1.0 m from an 18" diameter fan set to the highest setting. The following equipment and techniques will be used:

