### 5.3 Research protocol

#### 5.3.1 Description of the visits

Upon awakening the day of a study visit, participants will be asked to swallow an ingestible telemetric pill which will have been provided to them beforehand. Upon arrival to the laboratory, participants will be asked to provide a urine sample, self-insert a rectal temperature probe and weigh themselves nude (in private). Participants will then be instrumented following which they will rest in the seated position for a 10 min baseline period at a room temperature of 24°C. Following this baseline period, they will enter an environmental chamber maintained at either 38°C and 60% RH or 46°C and 10% RH and will be seated on a mesh chair that will allow for convective airflow. Participants will remain seated for 3 hours within the environmental chamber while the relevant cooling intervention is administered. During the exposure, heart rate will be measured continuously from an ECG signal and blood pressure measurements will be taken every 20 minutes by automated auscultation of the brachial artery. Rate pressure product (**RPP**) will subsequently be calculated at baseline and every 10 minutes during the 3 hour exposure (see arrows in timeline below). Participants will be provided with 3 ml/kg of water every hour. At the end of the 3 hour period, participants will exit the environmental chamber to be de-instrumented and will be asked to weigh themselves nude in private to calculate whole-body sweat rate. During the study visits with fan use, an 18" diameter fan will face the participant from a distance of 1.0 m to provide an airflow of 4.0 m/s. During the study visits with skin wetting, tap water (~18°C) will be sprayed to the forehead, face, arms, lower legs and neck with a bottle every 5 minutes.

[figure not shown]

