## Summary of changes

1) USyd 2018-496: Use of fans and/or skin-wetting as a low cost cooling strategy for older adults during heatwaves

| Date       | Modifications                                                                                                                                                                                                                                                                                                                                                                  |
|------------|--------------------------------------------------------------------------------------------------------------------------------------------------------------------------------------------------------------------------------------------------------------------------------------------------------------------------------------------------------------------------------|
| 11/09/2018 | 
 
- Edited total time for experimental study from 2hr to 3 hr
 
- Updated ambient conditions in hot dry heatwave to 45°C, 15% RH
 
- Included measure of Urine specific gravity on arrival to laboratory to measure dehydration
 
- Updated total time for the study
 
                                      |
| 15/10/2018 | 
 
- Added blood collection at a pathology clinic if approved for study by study physician
 
Removed measure of body composition
 
- Modified the administration of water consumption, from 200 ml every 20 minutes to 3 ml per kg of body weight per hour
 
- Updated total remuneration for participants
 
 |
| 19/11/2018 | - Updated recruitment flyer                                                                                                                                                                                                                                                                                                                                                    |
| 22/08/2019 | -Added researchers: [name], [name], [name] and [name] to the study                                                                                                                                                                                                                                                                                  |

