## 2 STUDY DESCRIPTION

### 2.1 Study Design

The study took place at two sites (Montreal and Sydney). Study participants were asked to volunteer for 1 preliminary visit, 1 screening visit and 4 to 8 study visits. During the study visits, participants were to enter an environmental chamber maintained at either 38°C and 60% relative humidity (RH) (typical North American heatwave condition) or 45°C and 15% RH (typical Australian heatwave condition). For each study visit, the participants were to remain within the environmental chamber and rest in a seated position for 3 hours under various conditions (cooling strategies). In Montreal, the 6 study visits were the following:

- 1) 38°C and 60% RH, no intervention (control)
- 2) 38°C and 60% RH, with fan use
- 3) 38°C and 60% RH, with skin wetting
- 4) 38°C and 60% RH, with fan use and skin wetting
- 5) 45°C and 15% RH, no intervention (control)
- 6) 45°C and 15% RH, with skin wetting.

In Sydney, participants were recruited for 2 preliminary visits and the 4 experimental visits under the North American heatwave exposure with the various cooling strategies. They were also provided with the option of doing additional visits that would be carried under the Australian heatwave exposure with the 4 cooling strategies, resulting in 2 additional visits compared to Montreal:

- 7) 45°C and 15% RH, with fan use
- 8) 45°C and 15% RH, with fan use and skin wetting.

In Montreal, participants were to first undergo the 4 study visits for the simulated North American heatwave exposure to minimize attrition for the primary objective. Participants were subsequently to undergo the study visits for the simulated Australian heatwave exposure. Within each heatwave exposure (North American, Australian) the sequence under which participants would undergo the study visits was randomized. In Sydney, participants were to undergo the 8 study visits in a randomized sequence. Prior to each visit, participants were asked to refrain from strenuous physical activity, alcohol, and caffeine for 12 h. To ensure there is no carry-over effect, study visits were to be performed on separate days, with at least 72 h between visits. Participants prescribed calcium channel blockers were asked to withhold this medication for 48 hours prior to each study visit.

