## **4 EFFICACY ENDPOINTS**

### **4.1 Primary Efficacy Endpoint**

The primary endpoint will be the change in rate pressure product (heart rate x systolic blood pressure) from baseline (pre-exposure) to the end of a 3-hour simulated heatwave exposure.

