## 5 STATISTICAL METHODOLOGY

### 5.1 Statistical Considerations

Statistical analyses will be performed using SAS Version 9.4 or higher. Unless otherwise specified, all statistical tests will be two-sided and performed at a significance level of 0.05.

Prior to all parametric analyses, basic assumptions will be checked and if they are violated, non parametric analyses will be performed to confirm results from the parametric analyses. If outliers are identified, analysis with and without the outliers may be presented.

In the event that a participant did not complete the 180 minutes heatwave exposure, the change from baseline will be calculated using the last measure available.

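### The Montreal protocol and the SAP give different hot-dry exposures for the same Montreal visits (46°C/10% RH and 45°C/15% RH), and the pooled secondary analysis depends on which was delivered

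*Supplement*

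**What the plan says.** **Hot-dry climate, Montreal.** The latest Montreal protocol uses 46°C/10% RH throughout: secondary objective (3.2), secondary outcome (3.5), the objectives table, the visit list (5.1), the visit description (5.3.1: "they will enter an environmental chamber maintained at either 38°C and 60% RH or 46°C and 10% RH") and the secondary analysis (6.2). The Montreal entries in the Summary of changes cover fluids, the rectal probe, the diabetes criterion, the chair, blood-pressure frequency and the skin-wetting method. None concerns the climate.

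**Hot-dry climate, Sydney.** The latest Sydney protocol uses 45°C/15% RH (2.1 and 4.6).

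**Hot-dry climate, SAP.** Section 2.1 describes a chamber at 38°C/60% RH "or 45°C and 15% RH (typical Australian heatwave condition") and lists Montreal visits 5 and 6 at 45°C/15%. The same label appears in the secondary objective (2.2), the secondary analysis (5.2.2) and the hot-dry beta-blocker analysis (5.2.3). The 5.2.2 model has a condition term and repeated measures, with no site or climate term.

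**Duration.** Sydney 4.4 states the primary endpoint as "change in rate pressure product from baseline to the end of a 2 h simulated heatwave exposure". Sydney 4.6 has participants "seated unrestrained in a standard armchair for the remainder of the 3-hour experimental protocol" after 30 minutes of baseline. SAP 4.1 measures the change "from baseline (pre-exposure) to the end of a 3-hour simulated heatwave exposure".

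**The concern.** The SAP combines two studies and analyses all hot-dry visits as one exposure. If both documents are followed as written, Montreal delivers one climate and the SAP reports another.

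Four consequences follow if Montreal ran at 46°C/10%:

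- Climate and site coincide exactly in the control and skin-wetting conditions, so the pooled contrast averages two climates with weights set by recruitment.
- Both hot-dry fan conditions come from Sydney only (SAP 2.1, visits 7 and 8), so the three contrasts in 5.2.2 would rest on different mixtures of climate.
- The hot-dry beta-blocker analysis is restricted to CAD patients. Sydney's criteria are evidently meant to keep out CAD and do exclude beta-blocker users, so this analysis is essentially Montreal-only and its 45°C/15% label would be wrong.
- The secondary objective, which names 45°C/15%, would be answered partly with data from another exposure.

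If Montreal instead ran at 45°C/15%, its protocol and amendment record do not show the change. Either way, the exposure behind the secondary result cannot yet be reported reliably.

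**Working it through.** **Step 1. Passages side by side.**

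| Item | Montreal protocol (latest) | Sydney protocol (latest) | SAP |
|---|---|---|---|
| Humid exposure | 38°C/60% | 38°C/60% | 38°C/60%, both sites |
| Hot-dry exposure | 46°C/10% | 45°C/15% | 45°C/15%, both sites |
| Exposure time | 3 h | 2 h (4.4); remainder of a 3-hour protocol (4.6) | 3 h, both sites |

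The humid climate agrees everywhere, so the climate conflict does not reach the primary analysis. It reaches SAP 5.2.2, the hot-dry part of 5.2.3, and the hot-dry runs of 5.2.4 and 5.2.5.

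**Step 2. The plan's own figures.** Montreal: a paired t-test with difference 1250, SD 2000, two-sided 0.0167 and n = 30 gives power 80.5% (stated 80%), and 30/0.9 = 33.3, rounded up to 34 as stated. Sydney: f = 0.5, alpha 0.05 and power 0.90 give 45 as stated if the numerator df is 1 (the protocol does not give the df). 45/0.8 = 56.25, against a stated 56. Neither calculation contains chamber setting or duration, so reconciling the text changes no sample size by itself.

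**Step 3. How different the two climates are.** Saturation vapour pressure in kPa: es(T) = 0.6108 × exp[17.27T/(T + 237.3)].

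- Air at 46°C/10%: 10.086 × 0.10 = 1.009 kPa
- Air at 45°C/15%: 9.582 × 0.15 = 1.437 kPa

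Evaporation from wetted skin depends on the skin-to-air difference. The documents give no measured skin temperature for these exposures. The Montreal literature review puts skin at about 35°C, which is taken here as an assumption: es(35) = 5.623 kPa.

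- Vapour gradient at 46°C/10%: 5.623 − 1.009 = 4.61 kPa
- Vapour gradient at 45°C/15%: 5.623 − 1.437 = 4.19 kPa, lower by 0.43/4.61 = 9%
- Dry-heat gradient: 46 − 35 = 11°C against 45 − 35 = 10°C, also 9% lower

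Range over the assumption:

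| Skin | Vapour gradient, 46°C/10% | Vapour gradient, 45°C/15% | Reduction | Dry gradient | Reduction |
|---|---|---|---|---|---|
| 34°C | 4.31 kPa | 3.88 kPa | 10% | 12 vs 11°C | 8% |
| 35°C | 4.61 kPa | 4.19 kPa | 9% | 11 vs 10°C | 9% |
| 37°C | 5.27 kPa | 4.84 kPa | 8% | 9 vs 8°C | 11% |

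At 45°C/15% there is less capacity to evaporate and less dry heat gain. The two act in opposite directions on net heat load, and the documents give nothing that converts either into rate pressure product.

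**Step 4. Duration.** The Summary of changes records "Edited total time for experimental study from 2hr to 3 hr", Sydney sessions now last about 4 hours (4.6), and the SAP describes 3 hours in the chamber for every visit. The sample-size paragraph in 4.4 matches the superseded Sydney protocol. That earlier protocol described seating for what remained of a 2-hour protocol and called the same thing a 2 h exposure. On that usage, the current wording in 4.6 means 180 minutes in the chamber, and 30 minutes of baseline plus 180 minutes fits a 4-hour session.

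**The case against.** **The mismatch concerns only secondary and exploratory results.** This stands. It is the main reason the point is not rated higher.

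**The comparisons are within participant, and the SAP already plans estimates by site.** Largely true. A participant's own control versus skin-wetting contrast is not biased by the other site's climate, and SAP 5.2.4 gives condition effects within Montreal and Sydney for each heatwave exposure. Two limits remain. Those estimates are exploratory, while the pooled one is the secondary result. Also, because Montreal has no hot-dry fan visits, a mixed model without a site term can use between-participant information, so Montreal's control data can influence the fan contrasts as well.

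**A reader might infer that the primary analysis mixes 2 h, 150-minute and 3 h exposures.** On that reading, the SAP rule that if "a participant did not complete the 180 minutes heatwave exposure, the change from baseline will be calculated using the last measure available" would apply to every Sydney visit. The documents do not support this. The Sydney procedure, the session length, the change record and the SAP all point to 3 hours, and the 2 h in section 4.4 looks like text that was not updated. It should be corrected, but it is not evidence of a shorter exposure.

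**A reader might also take the ratio of ambient vapour pressures, 1.437/1.009 = 1.42, as the size of the problem.** It is not the relevant quantity. The skin-to-air gradient differs by about 9%.

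**Conclusion.** The hot-dry conflict is real and unresolved between two current documents. The documents do not show which climate Montreal delivered, and this review does not judge which is right.

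If it was 46°C/10%, the pooled secondary estimate for skin wetting averages two climates whose evaporative and dry-heat gradients each differ by about 9% (8 to 11% for skin at 34 to 37°C), and the CAD beta-blocker hot-dry analysis carries the wrong label. If it was 45°C/15%, the error lies in the Montreal protocol and its amendment record, and the pooled analysis is unaffected. The effect on rate pressure product cannot be computed from the documents.

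The 2 h text in Sydney 4.4 is a minor inconsistency, with no shown effect on the primary analysis. Rating: should fix.

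**What to change.** 1. Before analysis, check the Montreal chamber records for visits 5 and 6 and reconcile the Montreal protocol (3.2, 3.5, objectives table, 5.1, 5.3.1, 6.2) with the SAP.
2. State the delivered temperature and RH for each site in SAP 2.1, 5.2.2 and 5.2.3. Correct whichever document is wrong, with a dated amendment or deviation note.
3. If the sites differed, make the by-site control versus skin-wetting estimates from 5.2.4 the reported secondary result in place of the pooled one, base the fan contrasts on Sydney data, and relabel the hot-dry beta-blocker analysis.
4. Reconcile the 2 h in Sydney 4.4 with Sydney 4.6 and SAP 4.1, and state in 4.6 whether the 30-minute baseline lies inside or outside the 3 hours.

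The cost is a check of existing records and a short text correction. No new data are needed and no sample size changes.
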